## Abstract

**Background:**

Alzheimer disease has no known cure. As existing pharmacologic interventions only modestly slow cognitive decline, there is a need for new treatments. Recent trials of repetitive transcranial magnetic stimulation (rTMS) have reported encouraging results for improving or stabilizing cognition in patients diagnosed with Alzheimer dementia. However, owing to small samples and lack of a well-controlled double-blind design, the results to date are inconclusive. This paper presents the protocol for a large placebo-controlled double-blind study designed with sufficient statistical rigor to measure the efficacy of rTMS treatment in patients with Alzheimer dementia.

**Objective:**

The objectives are to (1) recruit and enroll up to 200 eligible participants, (2) estimate the difference in treatment effects between active treatment and sham treatment, (3) estimate the difference in treatment effects between two doses of rTMS applications, (4) estimate the duration of treatment effects among responders to active rTMS treatment, and (5) estimate the effect of dementia severity on treatment outcomes among patients receiving active rTMS treatment.

**Methods:**

We have designed our study to be a double-blind, randomized, placebo-controlled clinical trial investigating the short- and long-term (up to 6 months) benefits of active rTMS treatment at two doses (10 sessions over 2 weeks and 20 sessions over 4 weeks) compared with sham rTMS treatment. The study will include patients aged ≥55 years who are diagnosed with Alzheimer disease at an early to moderate stage and have no history of seizures and no major depression. The primary outcome measure is the change in the Alzheimer Disease Assessment Scale-Cognitive Subscale score from pretreatment to posttreatment. Secondary outcomes are changes in performance on tests of frontal lobe functioning (Stroop test and verbal fluency), changes in neuropsychiatric symptoms (Neuropsychiatric Inventory Questionnaire), and changes in activities of daily living (Alzheimer Disease Co-operative Study-Activities of Daily Living Inventory). Tolerability of the intervention will be assessed using a modification of the Treatment Satisfaction Questionnaire for Medication. We assess participants at baseline and 3, 5, 8, 16, and 24 weeks after the intervention.

**Results:**

As of November 1, 2020, we have screened 523 individuals, out of which 133 were eligible and have been enrolled. Out of the 133 individuals, 104 have completed the study. Moreover, as of November 1, 2020, there has been no serious adverse event. We anticipate that rTMS will considerably improve cognitive function, with effects lasting up to 3 months. Moreover, we expect rTMS to be a well-tolerated treatment with no serious side effect.

**Conclusions:**

This protocol design will allow to address both the rTMS active treatment dose and its short- and long-term effects compared with sham treatment in large samples.

**Trial Registration:**

ClinicalTrials.gov NCT02908815; https://clinicaltrials.gov/ct2/show/NCT02908815

**International Registered Report Identifier (IRRID):**

DERR1-10.2196/25144

## Introduction

### Background

Dementia is a growing problem in our society as life expectancy increases. The leading cause of dementia, Alzheimer disease, has no cure, with current treatment options limited to slowing the progression of cognitive impairment. Recent small-scale clinical trials of high-frequency repetitive transcranial magnetic stimulation (rTMS) have shown some improvement in the cognitive abilities of patients with mild to moderate Alzheimer disease [1-15], with effects that diminish over a period of 2 to 3 months [8].

Cholinesterase inhibitors are the current treatment mainstay for Alzheimer disease. These medications increase the excitability of cells that respond to acetylcholine. The most commonly used medication, donepezil, shows some benefits in 20% to 60% of patients [16], but a substantial and marked benefit in only 2.3% of patients [17]. A long-term follow-up study of donepezil showed no significant benefit compared with placebo for improving or preventing declines in activities of daily living among patients with Alzheimer disease [18]. Moreover, some patients discontinue these drugs owing to severe side effects [16,17]. Thus, better treatments are needed. A few recent studies have suggested that modulating cortical excitability through noninvasive brain stimulation using rTMS is a promising approach to treatment, either alone or in addition to cholinesterase inhibitors [1-15].

rTMS is a noninvasive nonpharmacological technique that is quick to administer and relatively easy for patients to tolerate, with no lasting side effects. It is a procedure in which a series of electric currents are pulsed through a coil placed on the scalp; they produce a time-varying magnetic field [19] that passes through the skull to the brain, wherein a small current is induced in the underlying cortical tissue. Low-frequency pulses (<5 Hz) seem to decrease cortical excitability through the well-described process of long-term depression, while high-frequency pulses (10-20 Hz) seem to increase cortical excitability and synaptic plasticity through long-term potentiation mechanisms [20-22]. Long-term potentiation has a role in synaptic plasticity and is regarded as one of the central cellular mechanisms of learning and memory [23]. rTMS at either low or high frequency has been studied as a potential treatment for a wide variety of neurological and neurodegenerative disorders (eg, depression, Alzheimer disease, Parkinson disease, and stroke). Currently, the use of rTMS is only approved for the treatment of major depressive disorders.

### Development of the Protocol

A few studies [1-8], including some from our team, have explored the possibility of rTMS as a treatment for Alzheimer disease in small samples (<45) with similar protocols, that is, high-frequency rTMS applied bilaterally to the dorsolateral prefrontal cortex (DLPFC). The assessments used in these studies mostly included Mini-Mental State Examination (MMSE) and Alzheimer Disease Assessment Scale-Cognitive Subscale (ADAS-Cog; some only used performance on an object/action naming task). They all reported some improvements over the course of treatment. Not every study had a sham-treated control group. Only one of these studies investigated the durability (up to 3 months) of the treatment among responders. None of these studies reported any adverse effect of the treatment.

To date, such studies have yielded conflicting results, which may be due in part to methodological limitations, such as a small sample size and the lack of a well placebo-controlled double-blind design. We aim to address these limitations in a large sample clinical trial investigating the efficacy of rTMS treatment and the duration of its effects. We will also explore the characteristics of responders and nonresponders.

Previous studies of rTMS in patients with Alzheimer disease used different rTMS protocols (ie, different areas of stimulation, duration and frequency of stimulation, coil type, number of pulses, and intertrain interval), without directly addressing their suitability for Alzheimer disease. The most important parameters of rTMS treatment are stimulation frequency and the location targeted by this stimulation. Many previous studies of rTMS treatment in the context of Alzheimer disease have used high-frequency (10-20 Hz) stimulation bilaterally to the DLPFC in order to increase cortical excitability. The DLPFC plays an important role in executive functions, such as planning, organization, and decision-making, with a well-established key role in working memory. Dementia commonly affects these cognitive processes, and it is related in part to DLPFC dysfunction [24]. Other studies have stimulated the Broca area, Wernicke area, parietal somatosensory association cortex, right frontal gyrus, right superior temporal gyrus, parietal P3/P4, posterior temporal T5/T6, and precuneus, and combinations thereof with varying degrees of success [9-15]. The only large study so far used neuroAD therapy applied over 6 weeks to six sites (three at a time and alternating across days). This study claimed a considerable improvement (ie, 31.7% had a 0-4 ADAS-Cog improvement for active treatment compared with 15.4% for sham treatment) in people with Alzheimer disease and baseline Montreal Cognitive Assessment (MoCA) scores less than 30 [14]. Weiler et al have reviewed the extant literature up to 2018 [25].

Individuals with Alzheimer disease may have profound impairment of metabolic interactions between neurons and astrocytes owing to an abnormal glutamate-glutamine (Glx) cycle [26]. Application of high-frequency rTMS to the left DLPFC area has been shown to increase Glx levels and normalize the Glx cycle [27]. High-frequency rTMS also increases cerebral blood flow and glucose metabolism in stimulated and remote brain regions [28], as well as reduces intracortical inhibition at the stimulation site [29]. High-frequency rTMS applied to the right DLPFC area has been shown to alleviate anxiety symptoms [30], which are considerably higher in patients with Alzheimer disease at mild to moderate stages than age-matched healthy controls [27,28,31,32]. Enhanced synaptic plasticity has been suggested as a potential mechanism for the effects of high-frequency rTMS [21].

Cortical excitability is observed following repetitive high-frequency stimulation [33,34]. Long-term potentiation–like changes in synaptic strength are widely presumed to be a mechanism of learning and memory. It has been shown that 100-Hz magnetic stimulation induces long-term potentiation effects in rat hippocampal slices [35], while related synaptic enhancement has been reported in cortical structures following 10 to 20-Hz stimulation [36,37]. High-frequency rTMS can considerably upregulate brain-derived neurotrophic factor (BDNF) levels [38], which decline within the hippocampus in patients with Alzheimer disease [39]. BDNF levels are affected by neuronal activity and long-term potentiation, which regulate these plasticity-related neurotrophins. Moreover, rTMS is a modifier of inhibitory neuron function. In hippocampal slices, 10-Hz stimulation reduces gamma aminobutyric acid (GABA)ergic synaptic strength in principal neurons. This supports models and mechanisms involving GABAergic synapses modulating the overall inhibitory/excitatory balance [40].

Building on this promising body of research, we chose to apply high-frequency rTMS bilaterally to the DLPFC. We speculated that this would benefit people with Alzheimer disease via enhanced blood flow and glucose metabolism, synaptic plasticity, and improved connectivity. Either side of the DLPFC will likely activate the basal forebrain cholinergic complex, which has projections over most of the cortex and has connectivity via GABAergic inputs to the midbrain regions. New studies have shown a link between GABAergic dysfunction and cognitive function [41-43]. Consequently, the increased excitability of these less GABA-suppressed areas in the brain of patients with Alzheimer disease may allow for increased response in not only cortical regions but also midbrain regions, which are important as major sources of cholinergic, serotonergic, and norepinephrinergic inputs to many regions of the brain.

The other parameters of rTMS treatment selected for this clinical trial, such as the number of pulses, intertrain intervals, and the duration of treatment, are rather arbitrary within a range [44]. They were selected from among specific parameters with demonstrated effectiveness in the extensive rTMS literature on Alzheimer disease [1-15], and depression as a depressive symptom is often comorbid with Alzheimer disease [45].

The intertrain interval in this trial was selected for its efficiency and safety profile as documented in international guidelines for the use of high-frequency rTMS [46,47]. Alternative stimulation protocols, such as theta-burst stimulation [44], are more efficient, but were not selected for study because there is only limited evidence for their effectiveness in Alzheimer dementia.

As for the choice of coil, there are only a few options. Double cone and H coils are used for reaching deep areas of the brain (up to 5-cm penetration), but they have not been used in Alzheimer treatment studies owing to the uncomfortable facial twitches that they may cause during high-frequency stimulation. As nearly all the studies cited herein use the figure-8 coil, this configuration was chosen. Pulses of both figure-8 and round coils penetrate only to the neocortex close to the skull surface of the brain.

### Choosing rTMS Parameters

The investigation of rTMS as a potential treatment for Alzheimer disease presents many challenges. Among these challenges is the multitude of parameters that may impact the efficacy of treatment, including, but not limited to, (1) the target area of stimulation, (2) the total number of pulses, which is also correlated with the duration of the treatment, (3) the frequency of the pulses, (4) the intensity of the pulses (percentage of the resting motor threshold [RMT]), and (5) the protocol of delivery of the pulses (train length, intertrain interval, etc).

Guerra et al considers managing the many variabilities in noninvasive brain stimulation studies [44]. To date, there is no study that can provide convincing answers as to what the optimum parameters are. For a tabularized review on the used rTMS parameters, please refer to a previous report [25]. Thus, we are still at the stage of pilot studies to determine an optimum protocol for Alzheimer rTMS treatment. One main constraint is the number of eligible study participants. This limits the number of protocols to be tested if we desire to have a high statistical power in our outcome measures. This study has endeavored to select reasonable and justifiable values for each of these parameters, mainly based on our previous pilot studies [8,48], which were themselves based on previous work in the field.

### Study Goal, Objectives, and Hypotheses

The overall goal of this study is to compare the efficacy of high-frequency active versus placebo rTMS for the treatment of cognitive impairment among people with mild to moderate Alzheimer dementia. The specific objectives and hypotheses of the study are as presented below.

First, estimate the difference in treatment effects among patients treated with active as compared with placebo high-frequency rTMS applied bilaterally to the DLPFC. Hypothesis 1 (H1) is as follows: better cognitive performance will be seen in patients randomly assigned to the active treatment group compared with those assigned to the placebo group.

Second, estimate the difference in treatment effects for patients receiving 4 weeks of rTMS versus 2 weeks of rTMS. Hypothesis 2 (H2) is as follows: four weeks of rTMS will be more effective than 2 weeks of rTMS in improving cognitive function.

Third, estimate the duration of treatment effects among responders to active rTMS, where response is defined as improvement in the ADAS-Cog of ≥3 points. Hypothesis 3 (H3) is as follows: treatment effects will still be detectable 8 weeks postintervention, although not necessarily at 16 and 24 weeks postintervention.

Fourth, estimate the effect of dementia severity on treatment outcomes among patients receiving active rTMS. Hypothesis 4 (H4) is as follows: the effect size will be greater in participants with a clinical dementia rating (CDR) of 1 than in those with a CDR of 2.

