### Treatment Protocol

Patients in both the active and sham treatment groups will undergo daily (5 days/week) rTMS treatment. Each treatment will apply 25 trains of rTMS pulses bilaterally to the DLPFC. Each train will have a duration of 1.5 s, and pulses will be applied at 20 Hz (for a total of 30 pulses per train). The intertrain interval will be 10 seconds. Thus, there will be a total of 1500 pulses delivered to the brain per day (25×30=750 per side), resulting in a total of 30,000 pulses applied over the course of 4 weeks of treatment (20 sessions) or 15,000 pulses for 2 weeks of treatment (10 sessions). Each TMS treatment session will take approximately 10 to 25 minutes. Any missed treatment sessions will be made up on the following day, with a minimum 30-minute break between sessions.

The pulses will be applied at 90% to 100% of the RMT of each participant. The RMT, which will be measured for each hemisphere before the first treatment, is determined by applying single TMS pulses over the primary motor cortex and observing the lowest intensity at which it causes an involuntary twitch of the participant’s contralateral thumb. The specific process involves setting the intensity of the stimulator at 65% to 75% of the maximum intensity and adjusting the coil location over the primary motor cortex until the “hotspot” for activating the involuntary twitch is found. Then, the intensity is lowered in 1% decrements to find the lowest intensity at which an involuntary twitch can be clearly observed in three consecutive pulses. The intensity of treatment will be 90% to 100% of the RMT, unless the participant is having trouble tolerating the treatment, in which case treatment at an intensity of 90% of the RMT will be used for the first session and increased to the full dose of 100% by the end of the first week of treatment.

The location of the DLPFC will be determined using the BrainSight 2 navigation system [52] for TMS. The right and left DPLFCs of each participant will be localized using their own MRI scan, and the coil location and direction will be specified using the BrainSight software at Talairach coordinates (x, y, z) = (–50, 30, 36). The coil will be held at approximately 45 degrees relative to the horizontal axis, but this will be measured approximately rather than specified exactly using the neuronavigation software.

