### Outcome Measures

Each participant will attend six assessment days in total as follows: baseline (week 0) and week 3, week 5, week 8, week 16, and week 24 posttreatment sessions. At each assessment day, three assessments will be given to the participant in the following fixed sequence: ADAS-Cog, verbal fluency test, and Stroop test. Only the patient and the research personnel designated to administer assessments will be in the room during assessments. At the baseline and week 5 and week 16 posttreatment assessments, additional caregiver assessments will be performed. Alzheimer Disease Co-operative Study-Activities of Daily Living Inventory (ADCS-ADL) and Neuropsychiatric Inventory Questionnaire (NPI-Q) assessments will be performed at each of these visits (in that order), while the Treatment Satisfaction Questionnaire for Medication (TSQM) will only be used at the week 5 assessment. These outcome measures must be administered to the same caregiver at each visit. If a participant is accompanied to an assessment visit by someone other than their usual caregiver, the assessor will contact the usual caregiver by phone to complete these assessments.

All assessments will be performed on a Monday or the first working day of the week. Note that the specific dates of the last three assessments (the follow-up assessments) will be adjusted based on whether the participant is in a 2-week or 4-week treatment group. An assessor will be assigned to each participant. That same assessor must perform all of the six assessments with the assigned participant. Deviations should be justified (changes in staff, assessor illness, etc), and an explanation will be documented in the assessment notes.

As participant schedules are often busy, we can adjust the specific dates of the assessments within ranges (Table 1). If no assessment is possible within these windows, the assessment will be skipped and the data point will be missing from the analysis (with the exception of the baseline assessment, which will require rescheduling the treatment).

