### Statistical Analysis

#### Sample Size Estimation

The sample size for the hypothesis that one group’s mean is statistically significantly different from the other (assuming two equally sized groups, which is the case in this study) can be calculated using the following formula [55]:

where *Z_α_* is the upper tail critical value in the standard normal distribution at the α level of significance (it is 1.96 and 2.58 for 5% and 1% significance levels, respectively), *Z_β-1_* is the normal deviate at 1−β% power with β% of type II error (it is 0.84 and 1.28 for 80% and 90% power, respectively), and *σ* and *d* are the standard deviation and difference of means of the two groups, respectively. The calculated N is the number of subjects in each group.

Using the above formula with a significance level of .05 (corrected using the Bonferroni adjustment for three treatment groups), an expected difference of 3 points on the ADAS-Cog score (derived from a study by Rabey et al [7], which also used ADAS-Cog as a primary outcome measure), a standard deviation of 4.9 points (derived from the results of our own pilot study [8]), and a power level of 80%, the minimum sample size is estimated to be 63 participants per group (189 in total). Allowing for 10% drop out, we will need to enroll at least 208 patients in the study to achieve this power.

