#### Analysis of the Results

Baseline characteristics will be assessed between the active and sham treatment groups by descriptive statistics, as well as formal statistical tests. Baseline differences between the two groups, if any, will be adjusted for in the final statistical analyses. All assessment scores will be checked for normality of distribution to determine the choice of either parametric or nonparametric methods. Bartlett statistic will be used to assess the homogeneity of variances, and Levene [56] or Brown-Forsythe [57] tests, which are less sensitive to departures from normality, may also be used. In all instances, a *P* value <.05 will be considered significant.

To test H1 and H2 (the efficacy of rTMS treatment), two-factor (active vs sham) repeated (pre-post treatment) analysis of variance (ANOVA) will be used to investigate the effect of treatment before and after the 4-week block of treatment. The dependent variable will be the change in the ADAS-Cog score (primary outcome measure). Testing H3 will be similar to the tests of H1 and H2, but the two factors will be the two durations of treatment.

For secondary outcome measures, a two-factor ANOVA will also be used in the same way as described above, but a Hochberg test [58] will be applied to correct for multiple comparisons.

The last-observation-carried-forward method will be used in the case of missing data or premature termination.

To test H4 (the durability of rTMS treatment), repeated measure ANOVA will be used among responders (those who show improvement in the ADAS-Cog score of ≥3 points over the course of treatment [3] in both groups) to investigate the duration over which the improvement may last. Post-hoc follow-up methods, such as Dunnett [59] and Tukey [60] tests, will be applied as needed. In addition, a mixed regression model will be developed to predict the response variable at each assessment visit of the active treatment group (both treatment arms separately). The independent variables will be patients’ current age and the severity of Alzheimer disease (as measured by the CDR).

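### The 4- versus 2-week comparison would be more precise if it adjusted for baseline and week-3 ADAS-Cog, which the stated pre-post ANOVA does not do

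*Protocol article*

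**What the plan says.** Study Goal, Objectives, and Hypotheses sets the aim to "estimate the difference in treatment effects for patients receiving 4 weeks of rTMS versus 2 weeks of rTMS" and numbers it H2. Analysis of the Results numbers it differently: "Testing H3 will be similar to the tests of H1 and H2, but the two factors will be the two durations of treatment". The test it refers back to is a repeated-measures ANOVA from before to after the 4-week treatment block, with change in ADAS-Cog as the dependent variable. Missing values are filled by last observation carried forward (LOCF).

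Under Treatment Protocol all arms have daily sessions, five days a week. The totals are 30,000 pulses over 20 sessions, or "15,000 pulses for 2 weeks of treatment (10 sessions". Under Outcome Measures ADAS-Cog is taken at weeks 0, 3, 5, 8, 16 and 24, and only "the specific dates of the last three assessments (the follow-up assessments) will be adjusted" for treatment duration. Table 1 gives week 3 a window of one day either side and requires week 5 to follow the final treatment. Under Randomization, participants are told how long their treatment will last.

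**The concern.** If weeks 3 and 5 count from the start of treatment, every active participant reaches week 3 after about 10 sessions. A 4-week participant seen a day late may have had one or two more. What is randomised between the active arms, stopping or continuing, takes effect only then. The week-3 score is therefore a second pre-divergence measurement of the primary outcome, already collected, and the duration test gives it no role. Nor does the test use baseline as a covariate rather than a subtracted value.

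Precision is at stake. Sample Size Estimation uses one expected difference of 3 points and gives none specific to 4 versus 2 weeks. A contrast between two active arms could well be smaller, although the article does not say so. Recruitment is also slow: 133 were enrolled by November 2020 against the 208 required.

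**Working it through.** **The plan's own figure.** Inputs from Sample Size Estimation: difference 3, SD 4.9, 80% power, a "significance level of .05 (corrected using the Bonferroni adjustment for three treatment groups", and printed critical values ("it is 1.96 and 2.58 for 5% and 1% significance levels, respectively"). The printed formula is not legible, so I use the standard one, n = 2 × SD² × (z_α + z_β)² / d² per group.
- α = .05/3 (z = 2.394): 48.02 × (2.394 + 0.84)² / 9 ≈ 56
- z = 2.58: 48.02 × 3.42² / 9 = 62.4, so 63

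The stated 63 matches the 1% critical value, not .05/3. That is a separate matter and does not affect this point. I keep 63 per arm.

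**Precision of the stated test.** Taking 4.9 as the SD of change, SE = 4.9 × √(2/63) = 0.873. The difference detectable with 80% power (exact t) is 2.47 points at two-sided .05 and 2.86 at .05/3. The normal approximation gives 2.45 and 2.82.

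**With baseline and week 3 as covariates.** The article gives no correlation, so the following is assumed. ADAS-Cog at weeks 0, 3 and 5 is a stable patient level (variance 36, 64 or 100), plus patient-specific change, plus independent visit noise, scaled so that the variance of change is 24.01 (24 in the first row). Detectable difference = 2.47 (or 2.86) × √(residual variance / 24.01).

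| Assumed source of change variance | Correlation of week-3 and week-5 change | Residual variance | Cut vs change score | Cut vs baseline adjustment alone | Detectable, .05 | Detectable, .05/3 | Power for 2 points, .05 |
|---|---|---|---|---|---|---|---|
| Half arises after week 3, rest noise | .35 | 20.9 | 13% | 10-12% | 2.3 | 2.7 | 68% |
| All visit noise | .50 | 17.2-17.7 | 26-29% | 18-22% | 2.1 | 2.4-2.5 | 75-77% |
| One quarter lasting change by week 3 | .62 | 14.4-14.5 | 40% | 35-38% | 1.9 | 2.2 | 83-84% |
| One half lasting change by week 3 | .75 | 10.4-10.5 | 56% | 55-56% | 1.6 | 1.9 | 93% |

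The change-score test has 62% power for 2 points at .05. A cruder check adjusts week-5 change for week-3 change only, so the variance factor is 1 − r²: a 9% cut at r = .3 and 64% at r = .8. Roughly 10-60% is a fair summary.

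**Is the stated test biased?** If the week-3 SD is also 4.9, a chance week-3 difference between the active arms has SE 0.87 (95% range about ±1.7). In a null simulation (8,000 runs, 63 per arm, r = .3 to .8), a fraction of about r of that difference passed into the unadjusted week-5 contrast and none into the adjusted one. Both estimates averaged zero and both tests held about 5% type I error.

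**A systematic week-3 difference.** This is possible because participants know their duration. In a 4,000-run simulation (one-quarter scenario) with a 1-point expectation shift by week 3 and no later effect, adjusting for both scores lowered false positives from 21% to 8% and bias from 1.0 to 0.4 points.

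**The case against.** The strongest reply is that this is an efficiency preference. Change from baseline between randomised arms is a valid contrast. A reader might infer that differences present before the arms diverge bias the dose effect or inflate type I error. For chance differences that is wrong: they are sampling error already counted in the standard error. This part of the objection stands in full.

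Covariates are often left to an analysis plan, and the article promises covariate analysis in general terms. That lowers the weight of the point, but the article does name the duration test, and that test gives week 3 no role.

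The timing is inferred. The abstract places the visits 3, 5, 8, 16 and 24 weeks after the intervention, which taken literally puts week 3 after all treatment. Outcome Measures and Table 1 favour counting weeks 3 and 5 from the start.

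Week 3 is also post-randomisation. If expectation moves week-3 scores, a model that forces equal active-arm means there is misspecified, so it should not be the only analysis.

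Three further inferences are not supported:
- That week 3 is never used: under LOCF it replaces a missing week-5 score.
- That precision is lost for 10 sessions versus sham at week 3: no such test of the 2-week arm alone is planned.
- That the mixed regression, meant to "predict the response variable at each assessment visit of the active treatment group (both treatment arms separately", harms H2: it predicts response from age and severity and does not contrast the arms.

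**Conclusion.** A cheap improvement, not an error in the test. On the supported reading of the schedule, adding baseline and week-3 ADAS-Cog cuts the variance of the 4- versus 2-week contrast by roughly 10-60% against change scores. The detectable difference falls from 2.47 to about 2.3-1.6 points at two-sided .05, or from 2.86 to about 2.7-1.9 at .05/3. This rests on SD 4.9 being the SD of change, on 63 per arm, and on correlations that the article does not give. The low end applies if much patient-specific change arises after week 3. Bias enters only through participants' knowledge of their duration, and adjustment reduces it without removing it. Nor does adjustment alter the fact that at week 5 the 2-week arm has been off treatment for about two weeks.

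**What to change.** Under Analysis of the Results, for the duration hypothesis at whichever later visit it is read:
1. Analyse ADAS-Cog in the two active arms by assigned duration, adjusted for baseline ADAS-Cog.
2. Prespecify a second analysis that also adjusts for week-3 ADAS-Cog, or an equivalent mixed model of the two active arms. The mixed model also handles missing scores and avoids LOCF presenting a 10-session week-3 score as a 20-session result.
3. Report the week-3 difference between the active arms as a check on expectation effects.
4. Use one hypothesis number for this comparison, and reconcile the abstract's visit timing with Outcome Measures and Table 1.

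The cost is wording only: no new visits, data or patients. The downside to state in the plan is that week 3 is post-randomisation. Analysis 2 therefore targets the added effect of sessions 11-20, while analysis 1 keeps the contrast of assigned 4 versus 2 weeks. Late week-3 visits in the 4-week arm may trim the second contrast slightly.
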